## 10.2 Recruitment for qualitative process evaluation

exclusion criteria of the main study continue to apply to patients participating in the process evaluation . Patients can optionally give their consent to be contacted for recruitment for the qualitative process evaluation on the consent form of the main study. Selected patients will be contacted by the qualitative researchers within a period of up to 1 year after completion of the intervention and, if they are interested, will be informed. Participating patients will receive a signed consent form and study information for the qualitative process evaluation.

Selected general practitioners , link workers , representatives of local services and members of the study team will be asked about their interest in participating in the qualitative process evaluation during and after the study via communication channels established within the study.

Inclusion criteria:

- Participants are adults capable of giving consent (18 years and older)

Exclusion criteria:

- Participants who are legally cared for in relation to their health

We aim to include n=30-40 participants in the qualitative process evaluation, half of whom will be participants in both study arms and half other study stakeholders. Sampling will be carried out step by step based on theoretical sampling until theoretical saturation is reached.

## 10.3 Data collection, data storage and data analysis for qualitative process evaluation

Based on the defined goals and topics of the qualitative process evaluation, interview guidelines are developed by researchers at the Charité Institute of General Practice and Family Medicine. In addition to the questions in the interview guide, socio-demographic information (age, gender, school education and occupation) is requested. The researchers conduct the interviews, record them and transcribe them. The interview takes place in person at the Charité's central campus, in the general practitioner's office, at the participants' homes or, at the participants' request, at a neutral location of their choice.

|                                  |                                   |                                                                                                         |                  |
|----------------------------------|-----------------------------------|---------------------------------------------------------------------------------------------------------|------------------|
| Version: V1.2                    | Last review:
February 12, 2025 | Created: [name], [name], [name], [name], [name] | Page
38 of 52 |
|                                  |                                   | Reviewed by: [name], [name]                                                    |                  |
| Release on:
February 12, 2025 | Next check:
N/A                | Released: [name]
Valid from: 04.09.2024                                             |                  |

|                   |                          |                                                                 |  |
|-------------------|--------------------------|-----------------------------------------------------------------|--|
| study
protocol | Study: „Soziales Rezept“ | Campus:
CCM                                                  |  |
|                   |                          | Scope:
Institute for General Practice and
Family Medicine |  |

In exceptional cases, a telephone interview is also possible upon request. The recordings and transcribed interviews are stored pseudonymously on a protected Charité internal drive. The interviews are evaluated using thematic coding (32) .

As part of the mixed methods approach, the qualitative interviews are recorded in parallel with the quantitative endpoints. The results of the evaluation are triangulated based on the quantitative and qualitative analyses of, among others, acceptance, practicability and need/use.

The concrete procedures for qualitative process evaluation are described in detail in the *SocPres\_SOP Qualitative Process Evaluation* .

## 11 Accompanying health economic evaluation

The feasibility study is accompanied by a health economic evaluation, which uses the quantitatively collected data from the study. The aim of this is, on the one hand, to check the acceptance of the survey instruments on well-being (ICECAP-A), quality of life (EQ-5D-5L) and resource utilization (PECUNIA RUM/EHIS- GeDA ). In addition, the link worker documentation is used to extract which offers were provided to patients and how the patient -link worker interaction went. The service utilization recorded is also evaluated in a group comparison in order to identify service areas with a significant group difference. The exploratory evaluations use the 5% and 10% significance levels. The findings will be used to revise the survey instruments for a follow-up study, i.e. to delete aspects in the PECUNIA RUM instrument that are less important in the application context of “social prescription” and to include the spectrum of offers provided outside the healthcare system for standardized documentation and determination of standard costs.

In addition to the results related to this research process, the data collected on service utilization as well as on quality of life and well-being are evaluated in terms of content. For the monetary assessment of resource use, the standard costs for all (privately purchased or prescribed) services and goods are calculated in euros. The cost-effectiveness of the intervention is determined using the net benefit approach. The statistical evaluation of the data will be carried out using parametric or non-parametric methods, depending on the distribution of the data. Finally, relevant subgroups from a health economic perspective will be identified and statements will be made on the power of the results achieved in order to support the sample size estimates for a potential follow-up study.

|                                  |                                   |                                                                                                         |                 |
|----------------------------------|-----------------------------------|---------------------------------------------------------------------------------------------------------|-----------------|
| Version: V1.2                    | Last review:
February 12, 2025 | Created: [name], [name], [name], [name], [name] | Page
39of 52 |
|                                  |                                   | Reviewed by: [name], [name]                                                    |                 |
| Release on:
February 12, 2025 | Next check:
N/A                | Released: [name]                                                                       |                 |
|                                  |                                   | Valid from: 04.09.2024                                                                                  |                 |

|                |                          |                                                              |  |
|----------------|--------------------------|--------------------------------------------------------------|--|
| study protocol | Study: „Soziales Rezept“ | Campus:
CCM                                               |  |
|                |                          | Scope:
Institute for General Practice and Family Medicine |  |

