#### 4.5 measures to reduce bias

##### 4.5.1 Randomization and Allocation

Randomization in this study is done to test the feasibility of randomization for the main confirmatory study. That is, randomization is not done with the aim of testing comparative hypotheses.

The randomization code is created by an independent person from the Institute of Social Medicine, Epidemiology and Health Economics (who is not otherwise involved in the study) as a block randomization (with variable block length) stratified by study center (general practitioner's practice) with an allocation ratio of 2:1.

All patients who consent to participate and meet the inclusion criteria will be randomized after the baseline assessment. The randomization codes will be taken from the REDCap database by the study

|                                  |                                   |                                                                                                         |                 |
|----------------------------------|-----------------------------------|---------------------------------------------------------------------------------------------------------|-----------------|
| Version: V1.2                    | Last review:
February 12, 2025 | Created: [name], [name], [name], [name], [name] | Page
22of 52 |
|                                  |                                   | Reviewed by: [name], [name]                                                    |                 |
| Release on:
February 12, 2025 | Next check:
N/A                | Released: [name]                                                                       |                 |
|                                  |                                   | Valid from: 04.09.2024                                                                                  |                 |

|                   |                          |                                                                 |  |
|-------------------|--------------------------|-----------------------------------------------------------------|--|
| study
protocol | Study: „Soziales Rezept“ | Campus:
CCM                                                  |  |
|                   |                          | Scope:
Institute for General Practice and
Family Medicine |  |

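### Section 11 plans the follow-up trial from two unreliable inputs: the power of the results achieved, and statistical significance as the only quantitative guide for revising the resource-use instrument

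*Protocol*

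**What the plan says.** Protocol Section 11 sets out a chain from this study to the next one. Besides checking acceptance of the instruments and drawing on link-worker documentation, it compares recorded service use between the arms "in order to identify service areas with a significant group difference". The thresholds follow: "The exploratory evaluations use the 5% and 10% significance levels". The use is then given: "The findings will be used to revise the survey instruments for a follow-up study", which includes the intention "to delete aspects in the PECUNIA RUM instrument that are less important in the application context" of social prescribing. No definition of importance is attached. The section closes by announcing that "statements will be made on the power of the results achieved in order to support the sample size estimates" for a possible follow-up study.

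Section 8.2 gives the size: 215 randomised 2:1 (143 and 72), about 30% drop-out, 150 with six-month data (100 and 50), and no formal sample size calculation. Section 8.1 makes all interpretation exploratory. Section 3 names data for planning a confirmatory trial, including its sample size, as part of the main objective.

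**The concern.** Both steps turn a result of this study into a design choice for the next one, so the exploratory label does not neutralise them.

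- **Power of the results achieved.** If this means power computed from the observed effect, it carries no information beyond the p-value. A noisy effect estimate would enter the next sample size under the name of power.
- **Significance as the marker.** A non-significant difference in a study of this size says little about whether an area differs. Even a true absence of difference does not make an area unimportant: a heavily used or expensive service can dominate mean cost and its variance in both arms. Section 11 plans a net-benefit analysis, which needs total cost, and a domain removed from the questionnaire cannot be recovered in the follow-up trial.

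**Working it through.** **Inputs from the protocol.** 215 randomised, 2:1, 30% drop-out (Section 8.2); alpha 5% and 10% (Section 11; taken as two-sided and unadjusted, since neither is stated). **Assumptions.** The protocol gives no effect sizes for service use, so those below are illustrations.

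**Step 1: the plan's own figures.** 215 × 2/3 = 143.3 and 215/3 = 71.7. With 70% retained: 143 × 0.7 = 100.1, 72 × 0.7 = 50.4, 215 × 0.7 = 150.5. The stated 100, 50 and 150 reproduce.

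**Step 2: power of the significance screen, continuous measure.** Power ≈ Φ(d/√(1/100 + 1/50) − z), with √0.03 = 0.1732 and z = 1.960 (5%) or 1.645 (10%).

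| Assumed difference (SD) | Power at 5% | Power at 10% |
|---|---|---|
| 0.2 | 21% | 31% |
| 0.3 | 41% | 53% |
| 0.5 | 82% | 89% |

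For 0.3 SD: 0.3/0.1732 = 1.732; Φ(1.732 − 1.960) = 0.410; Φ(1.732 − 1.645) = 0.535 (0.532 with the t distribution). Reaching 80% power needs 0.485 SD at 5%: (1.960 + 0.842) × 0.1732.

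**Step 3: the same for users of a service, 10% versus 20%.** Here the answer depends on which arm uses more, because the arms are unequal, and on the variance formula.
- Lower use under social prescribing (SP 10%, control 20%), pooled test: pooled proportion 20/150 = 0.133; null standard error √(0.133 × 0.867 × 0.03) = 0.0589; alternative standard error √(0.09/100 + 0.16/50) = 0.0640; Φ((0.10 − 1.960 × 0.0589)/0.0640) = 40%, and 52% at the 10% level. Unpooled: Φ(0.10/0.0640 − 1.960) = 35%, and 47%.
- Higher use under social prescribing (SP 20%, control 10%): pooled 32% and 46%; unpooled 40% and 53%.

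So a two-fold difference in use has power of roughly 32% to 40% at 5% and 46% to 53% at 10%.

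**Step 4: observed power.** With z_obs the normal quantile of the two-sided p-value, observed power at the 5% level is Φ(z_obs − 1.960) + Φ(−z_obs − 1.960). Nothing else about the data enters.

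| p-value | z_obs | Observed power |
|---|---|---|
| 0.05 | 1.960 | 50% |
| 0.10 | 1.645 | 38% |
| 0.30 | 1.036 | 18% |

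Its instability is large. If the true difference is 0.3 SD (true power 41%), simulated observed power at 100 versus 50 runs from 6% to 92% (5th to 95th percentile).

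**Step 5: what the study can supply instead.** With 150 patients (148 degrees of freedom, normal data assumed), the 95% confidence interval for an SD is 0.90 to 1.13 times the estimate. For the variance, and hence for the required N at a fixed target difference, it is 0.81 to 1.27 times. Skewed costs would be less precise.

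**The case against.** The strongest reply is that Section 11 never says non-significant areas are removed. The deletion criterion is importance in the context of social prescribing, and instrument acceptance and link-worker documentation also feed the revision. That is correct. A reader might infer a literal rule of deleting whatever misses significance; the text does not state one. What remains is that a significant group difference is the only quantitative marker offered, and nothing else quantitative says what makes an item less important.

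A reader might also infer a contradiction with Section 4.5.1, where "randomization is not done with the aim of testing comparative hypotheses". That passage explains why patients are randomised. It does not bar exploratory comparisons, and Section 8.4 plans several, so the two can stand together.

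A third tempting argument is multiplicity. The list in Section 6.4 has six comma-separated areas. Tested once each, taken as independent and with no true differences, the chance of at least one significant area is 1 − 0.95^6 = 26% at 5% and 1 − 0.90^6 = 47% at 10%. But a false positive only keeps an item, which costs questionnaire length and does not bias a later cost analysis. The 10% level likewise makes wrongful removal less likely than 5% alone.

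Finally, the power statements are only to support the sample size estimates, no calculation is named, and the English is a translation. This softens the point, but observed power remains the plain meaning of the wording. Details left to a statistical analysis plan would not repair it, because the protocol itself names this as a planning input.

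**Conclusion.** The point holds in limited form. Observed power is a poor basis for sizing the next trial, whatever the data show. Statistical significance is an unreliable guide for shortening the cost instrument: at the expected completer numbers, differences of 0.3 SD, or of 10% versus 20% use, are missed about half the time or more (47% to 68% across the cases worked). These percentages rest on assumed effects, unadjusted two-sided tests and the expected 30% drop-out; a difference of 0.5 SD would be missed only 18% (5%) or 11% (10%) of the time. That an area can matter for cost without differing between arms needs none of these assumptions.

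The consequence falls on the follow-up trial. The primary feasibility endpoints and patient safety in this study are untouched. Because supplying planning data is part of the main objective, the change is still worth making.

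**What to change.** Reword Section 11 in two places.

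1. **Instrument revision.** State that statistical significance will not be used to delete items. Define importance by share of users, contribution to mean total cost and to its variance, item missingness, and whether link workers refer to the service. The last two build on the acceptance check and the documentation that the section already uses. Report group differences in service use as estimates with confidence intervals.
2. **Sample size input.** Replace the sentence on the power of the results achieved by a commitment to report the SD, baseline to follow-up correlation, intracluster correlation and drop-out, each with a 95% confidence interval. Size the follow-up trial on a worthwhile difference fixed in advance, not on the observed one.

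The cost is a text amendment and a few descriptive tables. Service use, link-worker records and standard costs are already planned, so no new data collection is needed.

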### 8.2 case number estimate

Since this is an exploratory feasibility study without confirmatory hypothesis testing, no formal sample size calculation will be performed. Based on previous experience, we assume that the analysis of a total of 215 participants (in a ratio of 2:1: 143 in the SP arm and 72 in the TAU+ arm) is sufficient to descriptively determine the feasibility and acceptability aspects of the study and to obtain further information for planning the subsequent study.

A drop-out of approximately 30% is expected, so that follow-up data for secondary clinical endpoints of 150 patients (n = 100 in the SP arm and n = 50 in the TAU+ arm) will be available after 6 months.

|                                  |                                   |                                                                                                         |                  |
|----------------------------------|-----------------------------------|---------------------------------------------------------------------------------------------------------|------------------|
| Version: V1.2                    | Last review:
February 12, 2025 | Created: [name], [name], [name], [name], [name] | Page
33 of 52 |
|                                  |                                   | Reviewed by: [name], [name]                                                    |                  |
| Release on:
February 12, 2025 | Next check:
N/A                | Released: [name]                                                                       |                  |
|                                  |                                   | Valid from: 04.09.2024                                                                                  |                  |

|                   |                          |                                                                 |  |
|-------------------|--------------------------|-----------------------------------------------------------------|--|
| study
protocol | Study: „Soziales Rezept“ | Campus:
CCM                                                  |  |
|                   |                          | Scope:
Institute for General Practice and
Family Medicine |  |

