### 8.4 analyses

Primary endpoints: The proportion of participants in the intervention group who attended at least one appointment with the link worker and the proportion of participants who discontinued the study before the 6-month follow-up (dropout rate) will be analyzed descriptively, with frequencies and percentages, including 95% confidence intervals per treatment group. The comparison of the dropout rate between the treatment groups will be done descriptively and using logistic regression to determine possible influencing factors.

Secondary endpoints are analyzed descriptively (frequencies/percentages, mean/standard deviation or median/interquartile depending on scale and distribution, each with corresponding 95% confidence intervals).

Comparisons between treatment groups will be performed using logistic regression (binary endpoints) or analysis of covariance (continuous endpoints adjusted for baseline , if available), taking center into account.

Safety: Adverse events are analyzed descriptively (frequencies and percentages per treatment group).

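### Section 11 lets the distribution of the data choose the method, which permits rank tests for costs although net benefit needs the difference in mean cost

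*Protocol*

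**What the plan says.** Section 11 (accompanying health economic evaluation) sets out several analyses.

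- **Costs.** For the monetary valuation, "the standard costs for all (privately purchased or prescribed) services and goods are calculated in euros".
- **Cost-effectiveness.** "The cost-effectiveness of the intervention is determined using the net benefit approach".
- **Method.** The sentence directly after that one reads: "The statistical evaluation of the data will be carried out using parametric or non-parametric methods, depending on the distribution of the data". No test, estimator or target quantity is named.
- **Use of the results.** The section ends by saying that "statements will be made on the power of the results achieved in order to support the sample size estimates for a potential follow-up study".

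A separate analysis comes earlier in the section: "The service utilization recorded is also evaluated in a group comparison in order to identify service areas with a significant group difference". Its purpose is to shorten or extend the resource-use questionnaire. On error levels the section says: "The exploratory evaluations use the 5% and 10% significance levels".

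Outside section 11, section 8.4 plans "analysis of covariance (continuous endpoints adjusted for baseline , if available), taking center into account" for comparisons between arms. That is a mean-based method, but it is not said to cover costs. Section 8.1 leaves statistical details to an SAP, which was not available for this review.

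**The concern.** A rule that lets the observed shape of the data pick the method can also let it pick the quantity being compared. Net benefit is linear in the difference in mean cost and the difference in mean effect, so the cost comparison that belongs beside it is a difference in means. A rank test asks a different question, namely whether values in one arm tend to exceed those in the other.

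The two questions can have different answers here. A link worker adds a modest cost for most people in the social prescribing arm, while any savings on hospital or emergency care would sit in a few people. A rank test sees the first and gives little weight to the second. The cost comparison and the net-benefit result could then disagree within one report. Power statements based on the rank comparison would not size a follow-up trial for mean net benefit, and providing data to plan that trial is part of this study's main objective (section 3).

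**Working it through.** **Sample size available.** Section 8.2 randomises "in a ratio of 2:1: 143 in the SP arm and 72 in the TAU+ arm" and expects about 30% drop-out: 215 × 0.70 = 150.5, 143 × 0.70 = 100.1 and 72 × 0.70 = 50.4. This reproduces the protocol's 150 (100 and 50), the size used below.

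**Target quantity.** With λ the value placed on one unit of effect,

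incremental net benefit = λ × (mean effect SP − mean effect TAU+) − (mean cost SP − mean cost TAU+).

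Only arithmetic means enter, so a rank statistic cannot be put into this formula.

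**Inputs that the protocol does not give.** It states no cost mean, spread or admission rate. All cost inputs below are assumptions chosen to show a range.

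**Model 1: hospital tail plus link-worker cost.** Outpatient cost is gamma distributed, a hospital stay costs 4,000, and each SP participant carries a link-worker cost. Inputs are set so that true mean costs are equal. Tests are two-sided at 5%, with n = 100 versus 50.

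| Assumed inputs | True mean, TAU+ | True mean, SP | Rank test rejects |
|---|---|---|---|
| Outpatient 240; stays 10% vs 6%; link worker 160 | 240 + 0.10 × 4,000 = 640 | 240 + 0.06 × 4,000 + 160 = 640 | about 94% or more |
| Outpatient 240; stays 10% vs 8%; link worker 80 | 640 | 240 + 0.08 × 4,000 + 80 = 640 | 56–86% |
| Outpatient 600; stays 10% vs 6%; link worker 160 | 600 + 400 = 1,000 | 600 + 240 + 160 = 1,000 | 39–45%, sensitive to the assumed spread of outpatient cost |
| Outpatient 240; stays 10% vs 9%; link worker 40 | 640 | 240 + 0.09 × 4,000 + 40 = 640 | 22–32% |

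The Welch comparison of means rejected in about 5–7% in these settings. In the first row the rank test gave 93.7% and Welch 6.7% in 4,000 runs. The rank figure passes 98% when outpatient cost is assumed least spread. In 42–49% of runs with those inputs, the rank test was significant although the observed mean cost was lower in the SP arm.

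**Model 2: lognormal costs, 2,000 runs.**

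| Scenario (SP vs TAU+) | Rank test | Welch | Percentile bootstrap of the mean |
|---|---|---|---|
| Means equal at 1,000; log-SD 1.0 vs 1.2 | 23% | 8% | 11% |
| Means equal at 1,000; log-SD 1.0 vs 1.4 | 60% | 11% | 12% |
| Means equal at 1,000; log-SD 0.8 vs 1.4 | 87% | 13% | 13% |
| Medians equal at 600; means 826 vs 1,599 | 8% | 32% | 56% |
| Identical distributions | 4.5% | 4.2% | 7.7% |

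A normality test rejected in every run of every scenario, so a distribution check would lead to the non-parametric branch. The rank test can react strongly when mean costs are equal, and it can miss a nearly twofold difference in means. Its rejections in the equal-mean rows are not errors for its own null hypothesis, because the distributions do differ. They answer a different question. Mean-based methods also over-reject somewhat under strongly unequal skew (8–13%).

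**The case against.** The strongest reply is that the protocol does not prescribe a rank test. A non-parametric bootstrap of the mean difference fits the wording and suits net benefit. The net-benefit approach is stated on its own, and nothing says that a rank test replaces it. A reader might infer that rank tests are planned for costs; the text supports only that they are permitted. This part of the reply stands.

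Second, a reader might extend the point to the comparison of service use. That comparison is a screen to decide which questionnaire items matter, and a rank test does not contradict that aim. In a variant of model 1 without link-worker cost, the rank test rejected in 7–8% and Welch in 8–9%, so the two behaved alike. This also stands.

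Third, 94% could be taken as the size of the problem. It is one point in a wide range and follows from a flat link-worker cost of 160 set against an assumed outpatient mean of 240.

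Fourth, details go to the SAP and all results are exploratory (section 8.1). This limits the stakes but does not settle the matter. Section 11 already fixes a selection rule, and an SAP that follows it inherits the ambiguity.

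**Conclusion.** The point holds in a limited form. Section 11 makes the method depend on the distribution directly after committing to an analysis that needs mean differences. For skewed costs that permits a comparison which cannot support the net-benefit result or the planning of the follow-up trial.

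The size depends on assumed costs. With equal true means at 100 versus 50, rank-test rejection ran from roughly 20% to 98%, against about 5–7% for a comparison of means in the model with a hospital tail and 8–13% in the lognormal model with unequal skew. The direction of the problem is stable across these assumptions; its magnitude is not. The documents do not support the claims that rank tests will be used, that the service-area screen is flawed, or that any single percentage describes this trial. The correction is worth making because it is nearly free and the results are meant to inform the next trial.

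**What to change.** Replace the method sentence in section 11 with wording such as: Total costs, costs by category and net benefit are compared between arms as differences in arithmetic means, whatever the distribution, using a method robust to skew (for example a bias-corrected bootstrap, a generalised linear model or net-benefit regression) and taking centre into account; medians and rank tests for costs are descriptive only. Add that the power statements for a follow-up study refer to this mean-based comparison.

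The exploratory screen of service areas may keep its own method, named separately. The choice of interval can stay with the SAP. Resampling within arm and practice should not be made compulsory: with nine centres (section 4.6) and about 50 controls, cells would average 50 / 9 = 5.6 controls.

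The cost is one sentence and a little more analysis work, with no new data. The drawback is that bootstrap intervals can be somewhat liberal at this size; the percentile version rejected in 7.7% of runs with identical distributions.
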